### Inclusion criteria

Live or cadaveric donor.Informed consent form signed by the live donor or consent provided by the guardian or next-of-kin for a deceased donor.

### Exclusion criteria

Known allergies, including allergies caused by azithromycin.Severe heart, liver, or renal dysfunction or hematological, respiratory, cardiovascular, psychiatric, or metabolic disease within a 6-week period before transplantation.Use of hormonal or other medication, including macrolides.Concurrent participation in other clinical trials.

### Randomization

Participants will be randomly assigned to either the azithromycin or placebo group by using the method of random permuted blocks [21].

### Blinding

This is a double-blind trial; therefore, both the patients and the clinical practitioners will be blinded at all stages of the RCT. Furthermore, to prevent potential biases, other researchers, including data collectors and statisticians, will also be blinded to the trial.

### Interventions

Live donors in the azithromycin group will receive 1 g of azithromycin (four capsules of 250 mg) orally 1 day prior to surgery. Capsules will be opened, and the powder will be mixed with 10–15 mL of sterile water and immediately administered via a gastric tube in the case of deceased donors. The tube will be pre-flushed with 30 mL of sterile water; after administration, the tube will be flushed again with 30 mL of sterile water and clamped. The participants in the control group will receive a placebo. To ensure compliance, all live donors will ingest the capsules in the presence of a physician [22]. Possible side effects due to the azithromycin treatment will be monitored; to our knowledge, there are no contraindications for administering azithromycin through enteral feeding tubes [23]. In cases of serious side effects, the trial will be ended and treated.

### Immunotherapy protocols

Maintenance immunosuppression therapy in most recipients will consist mainly of cyclosporine. The majority of patients will also receive mycophenolate mofetil and prednisolone, except for those who experience side effects. All medical regimens will be recorded during hospital visits.

### Patient follow-up

Patients will be followed for 3 months after treatment. Clinicians will examine the patients every day for a week after surgery, and again at 1 and 3 months.

### Outcome measures

#### Primary outcome

The primary outcome will be the kidney graft function (evaluated using the glomerular filtration rate).

#### Secondary outcomes

Other studies have reported that prophylaxis with macrolides can decrease systemic inflammatory response syndrome [24, 25]. Chow et al. [24] reported that clarithromycin therapy reduced febrile response, tachycardia, tachypnea, and the strength and length of postoperative pain, and suppressed an increase in monocyte counts, concluding that macrolide treatment can yield improved clinical outcomes. Therefore, the secondary outcomes in our RCT will be the rejection rate, pain and systemic inflammatory response syndrome in donors, and complications and inflammatory responses in both donors and recipients.

Theoretically, azithromycin accumulated in the grafted kidney can decrease the rate of urinary tract infections (UTIs) after transplantation, because of the antimicrobial effect of azalide drugs. Azithromycin has been shown to inhibit UTIs caused by *Pseudomonas aeruginosa*, which are mainly catheter-associated UTIs [26, 27]; therefore, another secondary outcome in the study will be the incidence of UTIs in recipients.

### Outcome evaluation schedule

Outcomes will be assessed at baseline and at 1 and 3 months post transplantation. The patients will undergo routine blood tests, liver function tests, and kidney function tests. The overview of the outcome evaluation schedule is shown in Fig. 1.

### Assessment of adverse events

According to previous RCTs, azithromycin administration may cause several types of adverse events, including hearing loss, cardiac arrhythmia, nausea, and vomiting [28]. Adverse events will be carefully recorded in case report forms.

### Statistical analysis

We will use standard descriptive statistics to assess baseline clinical and laboratory data at enrollment. Subsequently, we will compare creatinine levels at the end of each study period by using mixed models for repeated measures. Fixed factors will include the degree of human leukocyte antigen mismatch, age, sex, etiology of and baseline comorbidity, medication (azithromycin or placebo), and baseline laboratory test parameters (inflammatory and non-inflammatory markers). Complications, UTIs, and other outcomes will be similarly evaluated. Nominal data will be compared using the Student’s T test and categorical data will be compared using the χ^2^ test. Patients who drop out during the study period will be analyzed until the last hospital visit at which data are collected. *P* < 0.05 will be considered as a significant level. All data will be analyzed using SPSS software Version 20.

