**Methods:**

This study is a single-center, randomized clinical trial. A total of 60 kidney donors will be randomly allocated to the azithromycin or placebo group and treated with a single dose (1 g) of azithromycin or placebo, respectively, 1 day before surgery. Recruitment commenced in September 2016 and is expected to be completed by March 2018. The primary outcome is kidney graft function. The secondary outcomes include rejection rate, urinary tract infections in graft recipients, pain and systemic inflammatory response syndrome in live donors, and complications in both donors and recipients. Outcomes will be evaluated at baseline and every day in the first week after transplantation, as well as at 1 and 3 months post transplantation. Adverse reactions will be documented. If the efficacy of azithromycin in reducing adverse outcomes is confirmed, it would serve as an easy to use, economic intervention able to lower post-transplantation risks.

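### Graft function has no primary time point: it is compared at each undefined study period at P<0.05, and the article gives two different outcome schedules

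*Protocol article*

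**What the plan says.** Under Primary outcome, the article states: "The primary outcome will be the kidney graft function (evaluated using the glomerular filtration rate". No visit, change rule or averaging rule follows.

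Under Statistical analysis, the comparison is made on creatinine: "we will compare creatinine levels at the end of each study period by using mixed models for repeated measures". The term for the period is not defined there or elsewhere. The model description begins "Fixed factors will include the degree of human leukocyte antigen mismatch, age, sex, etiology of and baseline comorbidity" and ends "medication (azithromycin or placebo), and baseline laboratory test parameters (inflammatory and non-inflammatory markers". Neither visit nor medication-by-visit appears in the list. The error rule is that P below "0.05 will be considered as a significant level".

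Two places say when outcomes are measured:

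- Abstract, Methods: "Outcomes will be evaluated at baseline and every day in the first week after transplantation", and then at 1 and 3 months.
- Outcome evaluation schedule: "Outcomes will be assessed at baseline and at 1 and 3 months post transplantation".

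Participants and Patient follow-up both describe clinical examinations daily for a week and then at 1 and 3 months. They agree with each other, but they concern examinations and not outcome assessments as such.

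**The concern.** The time point is part of the definition of a primary outcome. Without it, a favourable result at an early day, at month 1, at month 3 or averaged over visits could each be presented as the primary result once the data are known. The wording of the analysis invites this, because it announces a comparison at each period and ranks none of them. The conflicting schedules add to the problem, since a reader cannot tell how many comparisons there are.

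The measure is also unsettled. The outcome is defined by GFR and the analysis is run on creatinine, so even a named visit would leave two candidates for the primary result.

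At stake is either a type I error above the stated 5% for the only primary outcome, or a claim whose time frame is unclear.

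**Working it through.** The article states no power or familywise error for this outcome, so it has no figure to reproduce. The check counts the comparisons under each schedule and works out the error under each reading of the analysis.

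**Inputs from the article**

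- Level 0.05 for every test, with no adjustment stated (Statistical analysis). Sidedness is not given; two-sided is assumed.
- Post-transplant assessments under the Abstract: 7 daily + month 1 + month 3 = 9.
- Post-transplant assessments under the Outcome evaluation schedule: month 1 + month 3 = 2.

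**Assumption.** The article gives no between-visit correlation, so a range of 0.5 to 0.9 is used, either exchangeable or AR(1) by visit order.

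**Reading A: each period is tested at 0.05**

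If the tests were independent, P(at least one false positive) = 1 − 0.95^k:

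- k = 2: 1 − 0.95² = 0.0975
- k = 9: 1 − 0.95⁹ = 0.370

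Repeated measures on the same recipients are correlated, which lowers these values. The table comes from simulating k jointly normal test statistics with mean zero (400,000 draws) and counting draws in which any |z| exceeds 1.96.

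| Correlation | k = 2 | k = 9, exchangeable | k = 9, AR(1) |
|---|---|---|---|
| 0.5 | 0.091 | 0.269 | 0.327 |
| 0.7 | 0.084 | 0.203 | 0.277 |
| 0.9 | 0.070 | 0.124 | 0.174 |

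With k = 2 the two structures coincide. The error is therefore about 7-9% with two assessments and about 12-33% with nine. Treating week 1 as a single period would give k = 3 and about 8-13% (exchangeable: 0.083 at 0.9, 0.110 at 0.7, 0.125 at 0.5). The article does not define such a grouping.

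**Reading B: the medication main effect is the only test**

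This is one test, so the error is 0.05. The estimate is a weighted average over visits, and the weight on month 3 depends on the schedule and the covariance:

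- Two assessments, equal variances: 1/2 = 50%.
- Nine assessments, equal weights (exchangeable): 1/9 = 11%.
- Nine assessments, AR(1), complete data and equal variances: the weight of the last visit is 1/(9 − 7ρ). This gives 1/5.5 = 18% at ρ = 0.5, 1/4.1 = 24% at 0.7 and 1/2.7 = 37% at 0.9.

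**Comparison of the readings.** A and B are alternatives. A raises the error rate without averaging over visits. B averages over visits without raising the error rate. The article does not say which is meant.

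**The case against.** **The article is a condensed protocol.** An analysis plan that is not shown may hold the model terms and more. This stands for the model terms. A reader might infer that the listed model cannot produce per-period comparisons because visit and medication-by-visit are absent. The text does not support that: the list is introduced as what the factors will include, which need not be exhaustive, and a repeated-measures comparison at each period presupposes a time factor. The absence of those terms is a reason to state them and is not in itself an error. The objection does not reach the rest. The article itself sets a rule of comparing at each period at P<0.05, gives the primary outcome no time point, and prints two different schedules.

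**The averaging may be harmless.** A reader might infer that a week-1 effect would pass for 3-month function, citing 7 of 9 records (78%) from week 1, or a 10 mL/min effect confined to month 3 shrinking to 10/9 = 1.1 mL/min. Those figures hold only with nine assessments and equal weights. Under AR(1) the same effect would appear as about 1.8 to 3.7 mL/min, and with two assessments as about 5. An effect confined to month 3 also sits poorly with the article's rationale, which expects the drug to persist in tissue for up to a month. Besides, the model described is for creatinine, which is not on a mL/min scale. No single dilution figure is supported.

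**This is a pilot.** The Sample size section calls the trial a pilot and appeals to precision of estimates. That softens the case for strict familywise control. It does not remove the need for one primary contrast, because the analysis sets a significance level and the Abstract speaks of efficacy being confirmed.

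**The 90-day horizon.** The Discussion mentions evaluating graft function over 90 days. That is a duration named within a limitation and not a declared primary time point.

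**Conclusion.** The concern holds in this form. The primary outcome has no time point, the analysis announces several comparisons at 0.05 with none designated as primary, and the two outcome schedules imply either two or nine post-transplant assessments. If each is tested, the chance of at least one false-positive graft-function result is about 7-9% or about 12-33% respectively. These ranges rest on assumed correlations of 0.9 to 0.5 and two-sided tests. If the medication main effect is the sole test, the error is 0.05, but the result is an average over visits and not the comparison announced. Inflation and averaging should not be charged together. The schedule conflict lies between the Abstract and the Outcome evaluation schedule only, and the text shown does not establish which of the two is right.

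**What to change.** Before unblinding:

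1. Name one primary contrast tested at P<0.05. Graft function at 3 months is a natural example, as it is the last visit under both schedules. Month 1 or a pre-specified average would also give a single test at 0.05, so the choice is the sponsor's.
2. State one measure, so that Primary outcome (GFR) and Statistical analysis (creatinine) agree.
3. State visit and medication-by-visit as terms of the mixed model, and take the primary contrast from that model.
4. Report the other visits as supportive, with confidence intervals.
5. Reconcile the Abstract with the Outcome evaluation schedule, and define the study period or drop the term.

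With one pre-specified contrast the type I error for graft function is 0.05. Keeping every visit as a primary test would instead need, under Bonferroni, 0.05/2 = 0.025 or 0.05/9 = 0.0056 per test.

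The change needs no extra recipients. The cost is that earlier visits can no longer carry the efficacy claim. Timing matters: Trial status expected the study to conclude in March 2018, so the date of the decision should be documented. If the data have already been unblinded, the choice cannot be presented as pre-specified.

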## Discussion

The strength of this trial is that it is a well-designed, novel, double-blind RCT. It will provide evidence of the effect of azithromycin on kidney transplantation outcomes. The secondary objectives will allow us to examine the effect of azithromycin on UTI rates in recipients and pain and inflammatory responses in both donor and recipients. Further, short and mid-term analyses of blood and urine samples as well as immunological assays will enable a more in-depth analysis of the effects of azithromycin on transplantation outcomes. On the other hand, the limitation of this trial is that the importance of graft function may be overestimated due to the evaluation of graft function for 90 days because of short-term drug influences.

## Trial status

Patient enrollment began in September 2016 and is still ongoing. The study is expected to conclude in March 2018. Final results from this RCT are expected in the second quarter of 2018. The results will be published in national and international peer-reviewed journals.

## Abbreviations

IL: interleukin
mTOR: mammalian target of rapamycin
RCT: randomized controlled trial
UTI: urinary tract infection
